### Safety

2.11

AEs will be recorded at each visit during the trial. A SAE refers to 1 of the following AEs:

(1)death or life-threatening condition(2)necessity of hospitalization or extension of hospitalization period(3)persistent or meaningful disability or deterioration of function(4)congenital malformation or abnormalities(5)other medically important situations.

In case of any event that is considered to have a significant effect on the safety and health status of participants, investigators and relevant experts will determine whether it is considered to be a SAE, and depending upon the medical decision, appropriate action will be taken accordingly.

Safety variables are AEs, vital signs, and laboratory tests. Safety variables will be measured on all the visits during the trial, and their frequency, onset, severity, and causal relationship with the use of drugs will be checked. For each group, the frequency of causal AEs and non-causal AEs will be recorded. Comparisons between groups will be made for the number of AEs and the proportion of participants who have experienced 1 or more AEs. Descriptive statistics will be presented on between-group comparison of vital signs and laboratory tests at before and after the administration of drug and their changes.

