#### Discontinuation criteria

2.4.4

Participants can be excluded from the study when any of the following conditions are met:

(1)In case the participant withdraws their consent to participate in the trial.(2)In case the participant violates the inclusion criteria or meets the exclusion criteria.(3)In case the participant has serious adverse events (AEs), or it is difficult to continue the clinical trial due to AEs.(4)In case it is judged impossible to continue treatment or observe the participant due to an unexpected disease or accident.(5)In case the participant requests discontinuation or the investigator determines discontinuation due to a worsening cognitive deficit during the clinical trial.(6)In case cognitive function deteriorates during the clinical trial and CDR becomes 1 or higher.(7)In case it is determined that there is an unavoidable reason for the participant to discontinue the trial.(8)In case overall compliance is less than 70%.

To promote compliance of participants, we plan to send a text message as a reminder a day before the appointment.

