### Sample size calculation

2.9

Since there were no previous clinical trials on *H placenta* for this indication, the results of previous studies on herbal medicines using MoCA scores^[36]^ were cited. According to the previous study comparing MoCA scores after herbal medicine or placebo treatment of patients with MCI, calculation using a standard formula^[37]^ yielded a sample size of 10 for each group, with 80% statistical power at 5% level significance (α=0.05, 1-β=0.8). Assuming a dropout rate of 30% considering the 8-week-long administration and follow-up period, the final sample size will be 15 for each group, 30 in total.

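### Vital signs and laboratory tests are to be measured at every visit, but the only summary named for them is before versus after treatment, which leaves the intermediate values unused

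*Protocol article*

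**What the plan says.** Section 2.11 (Safety) of the protocol article defines the set: "Safety variables are AEs, vital signs, and laboratory tests". On timing it says "Safety variables will be measured on all the visits during the trial". The summary it then names for vital signs and laboratory tests is descriptive: "between-group comparison of vital signs and laboratory tests at before and after the administration of drug and their changes". It names no other summary for these two variables.

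AEs have their own provisions in the same section. On collection: "AEs will be recorded at each visit during the trial". On analysis: "Comparisons between groups will be made for the number of AEs and the proportion of participants who have experienced 1 or more AEs".

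Three other sections bear on the point. Section 2.7 (Interventions) schedules two visits a week for 8 weeks after screening, 16 treatments in all. Section 2.4.4 (Discontinuation criteria) lets a participant be taken out of the study for harm: "In case the participant has serious adverse events (AEs), or it is difficult to continue the clinical trial due to AEs". Section 2.9 (Sample size calculation) plans 15 per group: "Assuming a dropout rate of 30% considering the 8-week-long administration and follow-up period".

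**The concern.** What is to be collected and what is to be summarised do not match. If vital signs and laboratory tests are obtained at every visit, a before/after comparison sets aside everything in between. Laboratory safety signals are often individual and temporary: one participant's value rises, is noticed, and returns to normal. A group mean of end minus start cannot show this. Nor does it show an abnormal value in someone who left without an end measurement.

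Safety is a stated objective of the trial (sections 2.1 and 2.2), and section 1 describes the prior human evidence for this treatment in cognitive disorder as a case study. A flat before/after table could therefore be read as more reassuring than it is.

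**Working it through.** **1. Meaning of before and after.** Section 2.11 does not give time points. Section 2.2 uses a similar phrase for symptoms around the 8 weeks of administration, and section 2.10 uses one for the change over the whole trial. Baseline versus end of treatment is therefore the natural reading. Before and after each injection session is possible but less likely.

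**2. Visits used by the named summary.** Inputs: 2 visits a week, 8 weeks, after screening (section 2.7).
- Treatment visits: 2 × 8 = 16, which agrees with the stated 16 treatments.
- Screening plus treatment visits (assumption: no separate end visit): 16 + 1 = 17. Used: 2. Unused: 17 − 2 = 15.
- If baseline is the first treatment visit and screening is not counted: 16 − 2 = 14 unused.
- If there is a separate end-of-treatment visit: 18 − 2 = 16 unused.

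On any of these counts, 14 to 16 visits at which the article says the variables are measured do not enter the named summary.

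**3. What a before/after mean can show.** Suppose one participant's laboratory value rises by D.
- If the rise is still present at the end, the mean change in an arm of 15 moves by D/15.
- If it has resolved by the end, the mean change moves by 0, whatever the size of D.
- If that participant has no end value, the contribution is also 0.

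**4. How many could lack an end value.** Inputs: 10 required per group, 30% dropout, 15 per group (section 2.9).
- The plan's own figure first: 10 / (1 − 0.30) = 14.3, rounded up to 15 per group, 30 in total. It reproduces.
- Expected dropout: 0.30 × 15 = 4.5 per arm, or 0.30 × 30 = 9 overall.

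This is an upper figure. It covers dropout for any reason and assumes that nothing is measured at withdrawal. The number expected to stop because of harm is not given.

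**5. Does AE reporting close the gap?** In part. A laboratory or vital-sign abnormality reported as an AE is counted in the between-group AE comparison, at whichever visit it occurs. However, section 2.11 gives no rule by which an abnormal value becomes an AE. A symptomless rise that resolves would be counted only if an investigator chose to report it.

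**The case against.** The strongest reply is that this is a condensed article. It names one descriptive summary and rules out no others, and by-visit listings, shift tables and worst-value tables are ordinary content of a full protocol or analysis plan, neither of which is shown. That stands as a limit on the wording: one can say that before/after is the only summary named, not that it is the only one that will be produced. It does not remove the point, because the article states both the collection schedule and a summary that does not use it.

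It can also be said that the article has the frequency, onset, severity and causality of the safety variables checked, and that these formally include laboratory tests and vital signs: "Safety variables will be measured on all the visits during the trial, and their frequency, onset, severity, and causal relationship with the use of drugs". Those attributes fit events better than measured values, and the sentence names no tabulation.

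Three stronger readings are tempting, and the document does not support them.
- **A reader might infer that participants stopped for harm leave the safety result.** They do not. AEs are recorded at each visit and compared between arms, with no restriction to completers, so the event that led to stopping is counted. The article also nowhere says that no final measurement is taken at withdrawal.
- **A reader might infer that the liver and kidney limits in section 2.4.3 cannot be detected during treatment.** This would need laboratory tests to be taken only twice and those limits to be re-tested as on-treatment stopping rules. The article says neither. The schedule figure is not available.
- **A reader might infer that only 10 of 15 per arm are expected to complete.** Ten is the number required by the sample size calculation. The expected number at 30% dropout is 15 × 0.70 = 10.5, and dropout has many causes.

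**Conclusion.** The point holds as a mismatch between collection and summary within section 2.11. Followed as written, the named summary uses 2 of about 17 visits and cannot show an abnormality that resolves before the end. Such a value, or one in a participant without an end measurement, enters the safety result only through AE reporting. At most about 4 to 5 of 15 per arm, for any cause, could lack an end value. A bias towards no harm is possible but not demonstrated.

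This rests on three assumptions: that before and after means baseline and end of treatment, that the all-visits sentence is accurate for laboratory tests, and that each arm has 15 participants as in section 2.9 (Table 2 gives 30 in total). If laboratory tests are in fact taken less often, the error lies in that sentence instead, and it still needs correcting.

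**What to change.** Keep the before/after summary of vital signs and laboratory tests, and state the time points that it compares. Add, by arm, for every participant who received at least one injection:

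1. the worst post-baseline value of each variable and its shift from baseline;
2. the number of participants with any post-baseline value above the limits already in the exclusion criteria (section 2.4.3: AST and ALT at 2 times, BUN and creatinine at 1.5 times the upper reference limit). These limits would serve for descriptive counting only, not as rules for managing participants.

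For participants who stop early, use the last available on-treatment value as the after value, and report how many values were obtained in this way.

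If laboratory tests are not taken at every visit, correct the all-visits sentence so that it agrees with the assessment schedule.

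The cost is two extra descriptive tables, built from data that the protocol says it already collects. No additional participants, visits or measurements are needed.

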### Data management

2.12

All data will be recorded electronically in electronic case report form. A basic clinical trial document refers to a document that allows individual or overall evaluation of the performance of the trial and the quality of data obtained from it. The basic clinical trial document includes all source documents, monitoring records, correspondence, and regulations. The investigator will keep the protocol, documents, approvals, and all other data related to the clinical trial in the document storage room of the IRB for 3 years from the date of completion. Documents whose retention period expires will be shredded or incinerated. Investigators will have access to the final data sets. Data sets will be housed at https://www.mytrial.co.kr/.

### Monitoring

2.13

Monitoring will be performed to protect the rights and welfare of participants, to confirm whether the reported data is accurate, complete, and verifiable against source documents, and to ensure whether the clinical trial is being carried out in accordance with approved protocols and applicable regulatory requirements. Monitoring will be conducted by a designated separate company and its staff through regular visits to the institution or over the telephone. When visiting, the monitor will basically check the original record, medication record, and data storage. The monitor will also examine the procedure of the trial and consult with the investigator if there is a problem. The plan includes initiation site visit, interim monitoring visit, and close-out site visit, which will be conducted by visiting the institution in principle.

## Discussion

3

The current study is planned to examine the effect and safety of *H placenta* treatment on the cognitive abilities and mood of individuals with MCI. To the best of our knowledge, there have been no clinical trials examining the effect of pharmacopuncture on cognitive decline in a population of patients with MCI.

There are some systematic reviews that have evaluated the effect of acupuncture on cognitive function in patients with MCI or dementia. A meta-analysis reported that acupuncture could be effective for Alzheimer disease. Acupuncture combined with donepezil improved the MMSE score and activities of daily living compared to donepezil alone. AEs were observed in 7 out of 3415 cases, demonstrating the low risk.^[38]^ Acupuncture combined with other therapies also improved MMSE scores of patients with vascular MCI.^[39]^

Even though the effect of respective acupoints is not elucidated in clinical studies, the acupoints selected were those most cited in previous studies regarding cognitive function. GV20 and ST36 were used in experiments to observe cell proliferation and neuroblast differentiation in the hippocampus using acupuncture and electroacupuncture in rats.^[40]^ In the experiment applying electroacupuncture in GV20, SAMP8 mice showed improved behavior in the Morris water maze test and changes in metabolite analysis observed using proton nuclear magnetic resonance spectroscopy.^[41]^ Acupuncture treatment in GV20 and 3 other acupoints improved the the Alzheimer's Disease Assessment Scale-Cognitive Subscale (ADAS-cog) score of Alzheimer's disease patients and significantly changed oxidative stress marker levels in cerebrospinal fluid, blood, and urine.^[42]^ Acupuncture treatment was performed on SAMP8 mice in acupoints such as CV12 and ST36, resulting in significant differences in Morris water maze test results, indicating improvement in cognitive function, and changes in cell number, cell proliferation, and the expression of aging-related genes in hippocampal areas such as the dentate gyrus and CA3.^[43–45]^ Another study evaluated the effect of *H placenta* pharmacopuncture treatment in CV12 in Aβ-infused mice and showed behavioral change in the Morris water maze test. It also demonstrated that the expression of intracellular IL-1β and TNF-α was reduced in the hippocampus, and the oxidative stress, microglia, reactive astrocyte, tau and presenilin 1/2 was suppressed.^[19]^ Comparing administering acupuncture in ST36 versus sham acupoints in Alzheimer's disease rat model, blood perfusion and glycol metabolism were found to be increased in the bilateral limbic system, bilateral temporal lobe, right amygdala, and right hippocampus on positron emission tomography scan.^[46]^ Patients with Alzheimer disease were treated using acupoint thread embedding in ST36 and 3 more acupoints once monthly for 6 months (n = 13), and the MMSE and ADAS-cog scores were significantly changed compared to those in the control group (n = 13) (MMSE *P* < .01; ADAS-cog *P* < .05); however, the activities of daily living score did not change (*P* > .05). The functional MRI findings showed that the underlying mechanism might be related to the frontal and temporal lobe, limbic system, as well as cerebellum.^[47,48]^ Electroacupuncture treatment on the same region showed changes in the temporal lobe, limbic system, cerebellum, claustrum, and lobus insularis on functional MRI.^[49]^ In this study, we adopted *H placenta* for pharmacopuncture treatment. Coupled with the effect of *H placenta*, the effect of acupuncture is expected to advance the memory enhancement effect.

We have designed the trial to simultaneously assess mood, sleep quality and quality of life of MCI patients as secondary outcomes. As mood change and sleep disturbance are reported rick factors for progression from MCI to dementia,^[50,51]^ management of mood- and sleep-related symptoms is necessary. In addition to the effect of *H placenta* on cognitive function, its effect on mood and sleep has been previously reported. *H placenta* improved the level of monoamines in brain^[52]^ and reduced depressive-like behavior by modulating oxidative stress.^[53]^ Several case reports regarding the effect of *H placenta* on insomnia have been published.^[54–56]^ Thus, we expect that the auxiliary effect of *H placenta* will be estimated in this trial.

We are suggesting a new administration route of *H placenta* to combine the effect of acupuncture and that of *H placenta* on MCI. By assessing multiple aspects of MCI patients, the data from this proposed study can contribute to expanding the scope of MCI management and prevention of dementia progression.

## Trial status

4

The study is registered with the Clinical Research Information Service (KCT0005368). This protocol is based on version 1.7 of 05 Aug 2020. First participant will be enrolled in September, 2020. We anticipate that the recruitment will be completed by October, 2020. The data set is summarized in Table 2.

**Table 2 T2:** Items from the World Health Organization trial registration data set.

Data category	Information
Primary Registry and Trial Identifying Number	CRIS, KCT0005368
Date of Registration in Primary Registry	02 Sep 2020
Source(s) of Monetary or Material Support	Korea Health Technology R&D Project through the Korea Health Industry Development Institute (KHIDI), funded by the Ministry of Health & Welfare, Republic of Korea
Contact for Public/ scientific Queries	SC ([contact])
Public Title	None
Scientific Title	Efficacy and safety of Hominis placenta pharmacopuncture on mild cognitive impairment: Randomized, Double blind, Placebo-controlled, Multi-center Trial
Countries of Recruitment	Republic of Korea
Health Condition(s) or Problem(s) Studied	Mild cognitive impairment
Intervention(s)	Active comparator: *Hominis placenta* pharmacopunctureSham comparator: Saline pharmacopuncture
Key Inclusion and Exclusion Criteria	Inclusion criteria: Male and female adults aged 50 to 80, who are diagnosed with mild neurocognitive impairment based on DSM-5, scored CDR 0.5 and voluntarily participated in the trial.Exclusion criteria: diagnosis of dementia, neurological disease, psychiatric diseases.
Study Type	Type of study: InterventionalStudy design: randomized; subject-assessor blind; parallel group; treatmentSealed envelopes; computer-generated random numbers
Date of First Enrollment	05 Sep 2020
Sample Size	30
Recruitment Status	Not yet recruiting
Primary Outcome(s)	MoCA-K
Key Secondary Outcomes	MMSE-DS, K-DRS, CDR, GDS, K-BDI-II, STAI, STAXI, ISI, EQ-5D, EQ-VAS, GQOL-D
